### 1. **Surfactant lipid composition and concentration (University of Southampton)**

Mass spectrometric analysis of molecular species compositions of phosphatidylcholine (PC), phosphatidylglycerol (PG) and phosphatidylinositol (PI) in small volume TA samples. We expect reduced surfactant concentration and altered composition in baseline samples taken immediately before surfactant administration. These would both change after surfactant is given, and we might be able to assess the ratio of exogenous to endogenous surfactant from these two different compositions. Analysis of sequential samples (8 hrs, 16 hrs, 24 hrs, 48 hrs and 72 hrs if still intubated) will provide an indication of exogenous surfactant turnover.

### 2. **Surfactant function (Imperial College, London)**

Surfactant function will be determined by measuring surfactant adsorption to the air: liquid interface in a Langmuir trough. We will measure the tensioactive properties of lung surfactant from patients' TA. We will investigate whether isolated surfactant will have compromised function by the inhibition of plasma proteins, and whether the function can be recovered after administration of supplemented surfactant. Maximum reduction of the surface tension over continuous compression: expansion cycles models the physiological breathing cycles of intubated patients and will be carried on a captive bubble surfactometer. Adsorption analysis of the equilibrium surface tension, together with kinetics of the process, will explore inhibition processes in surfactant function.

### 3. **Immunological assessment (University College London and University of Manchester)**

Immune cellular components will be profiled to depth and soluble fluids for soluble mediators including those that imply a bacterial or fungal co-infection. The volume needed would depend on the concentration of the cellular component. Fixed blood will be split into 3 and then to each, a cocktail of antibodies will be added to enumerate all T cell subsets and markers of their subtype and activation. B cell subsets and their antibody isotype will also be investigated. In a separate panel we will identify neutrophils, eosinophils, dendritic cells, monocytes and macrophages. These panels have already been validated on blood samples from patients with COVID-19 in Manchester. The proportions of cells identified will be compared to normal ranges

within each age group. We will be specifically looking at the neutrophil to lymphocyte ratio that is described to be inverted in patients with the disease.

The level of the immunomodulatory surfactant protein D (SP-D) in serum has shown to be a promising biomarker for lung inflammation (and hence low levels in TA), and we will quantify the level of SP-D in both TA and plasma using our established ELISA. We will also quantify the level of C-reactive protein in TA as a biomarker for blood contamination of surfactant together with total protein concentration. We have seen that an inflammatory response to infections can result in specific degradation dependent on the infectious agent. We will analyse the degradation of SP-D and its sister protein SP-A using SDS-PAGE and Western Blot analysis to evaluate if COVID-19 infection results in degradation.

#### 4. **Oxidative Stress/Redox Measurements**

The extent of local and systemic oxidative stress with associated modifications of surfactant composition, alterations in cell signalling (due to interference with nitric oxide and hydrogen sulfide-related cell function) and shifts in redox status following the increased production of reactive oxygen species (downstream effects of the “cytokine storm”) induced by SARS-CoV-2 will be characterised in aliquots of pulmonary secretions and blood. 0.5 mL of bronchial fluid and a total of 1.5 mL EDTA plasma will be used for these analyses. Plasma will be divided into three 500 µL cryovial aliquots directly after centrifugation, frozen in liquid nitrogen and kept at -20°C until analysis.

Oxidative stress, nitric oxide, hydrogen sulfide and other redox related metabolites and products of ‘reactive species’ interactions will be quantified by an array of analytical platforms including ELISA, gas-phase chemiluminescence, HPLC, IC-MS, and LC-MS/MS to determine the following readouts: 8-isoprostanes, malondialdehyde (TBARS), nitrite, nitrate, total nitroso species, thiosulfate, sulfate, total free thiols, free and bound low-molecular weight thiols (including cysteine, homocysteine, glutathione), sulfide and polysulfide species.

#### 5. **Surfactant phosphatidylcholine synthesis**

Infusion of stable isotope-labelled choline (methyl-D9-choline chloride) IV will provide a measure of surfactant PC synthesis and hence function of ATII cells. This would be incorporated into the phospholipid analysis. The concentration of *methyl*-D9-PC molecular species will determine if surfactant therapy enhances synthesis and secretion of endogenous surfactant PC and administration of the second and third doses of unlabelled exogenous surfactant at t=8 and 24 hours will permit calculation of endogenous and exogenous surfactant pool sizes by dilution of the endogenously labelled surfactant. The only additional workload here would be IV infusion of *methyl*-D9-choline chloride over 3 hours after the patient is intubated and before the first surfactant administration. Patients in the control group will receive *methyl*-D9-choline at a time equivalent to surfactant administration in the treatment group, followed by identical sample collection.

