### Summary of surfactant and D9choline administration and sample collection schedule for the experimental mechanistic analyses

[figure not shown]

1. Surfactant will be given after a variable period of stabilization following intubation and ventilation.
2. D9choline infusion will commence after intubation and ventilation and typically before the first surfactant nebulization – 3.0 mg/kg body weight over 3 hours.
3. Samples will be taken shortly before surfactant administration at the times indicated.
4. Lung samples – 20-50 ml saline by ET tube followed by closed deep suction tracheal aspirates. 5-10 ml recovery expected.
5. EDTA blood samples – 10 ml; Transfix blood sample – 9 ml.

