**CONTROL:** Each cohort of 3 patients (in the treatment arm) will have 2 patients acting as controls (5 patients per cohort; total control n=8). The protocol for the control arm will be identical to the treatment arm except for surfactant nebulization.

After each cohort has completed treatment (or equivalent time for controls), the investigators will pause to review the outcomes of the treatment based on the co-primary outcomes (PaO2/FiO2 ratio and Ventilation index at 48 hours), reported adverse events and any additional safety or feasibility considerations. Additional trial outcome data may be taken into account if considered important in the opinion of the principal and chief investigators or if requested by the DSMB or TSC.

The decision to progress may be: 1. increase dose to next cohort level according to planned schedule (see below); 2. decrease dose to previous cohort level according to planned schedule (see below); 3. decrease dose to alternative level (specifically for cohort 1); 4. maintain dosage at current level. If there is a substantial and sustained improvement in the outcomes of a cohort, the subsequent cohorts may continue with the same dose as the previous cohort. If no improvement is observed, the subsequent cohort may increase the dosage. Early and substantial improvement during administration of the drug, or adverse events thought to be a safety concern, may prompt the investigators to reduce the administered dose during the conduct of the study.

Decisions relating to trial progression and dose escalation/maintenance/reduction will be made by the TSC after review of data by the DSMB. The DSMB will meet immediately prior to the TSC in open session but may meet in closed session at the request of any members of the DSMB or TSC. The TSC will meet after the DSMB and receive a verbal update from the DSMB. The TSC will be the final arbiter of trial progression and dose escalation/maintenance/reduction decisions. The majority of the TSC and all members of the DSMB will be independent of the trial investigators and trial conduct. An extraordinary meeting of the DSMB may be convened if the investigators have any safety concerns. Such a meeting would make recommendations to the TSC on trial continuation/discontinuation. The trial will not be discontinued on the basis of lack of efficacy. The trial may be stopped early on the basis of safety or feasibility concerns.

[figure not shown]

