### **Infusion of *methyl*-D9-choline chloride**

Deuterated *methyl*-D9-choline chloride will be dissolved in water at 10 mg/ml and infused at a dose of 3 mg/kg body weight over 3 hours, initiated during the stabilization period between intubation and administration of the first dose of surfactant. This timing is chosen to avoid conflict with time-consuming process of surfactant nebulisation. *Methyl*-D9-choline incorporation into lung surfactant dipalmitoyl phosphatidylcholine (DPPC), the major surface-active component, will measure surfactant phospholipid synthesis. It will answer several mechanistic questions. These include:

- 2.) Is surfactant therapy associated with an earlier restoration of surfactant synthesis, indicating recovery?
- 3.) Does the synthesis analysis confirm a reduced number of ATII cells? Can incorporation results provide an estimate of the efficiency of nebulized surfactant delivery to the peripheral lung?

The MHRA have confirmed that *methyl*-D9-choline chloride is not an IMP. A metabolic pathway for *methyl*-D9-choline incorporation into PC is shown below, together with an example of the diagnostic mass spectrometry scans used for detection and quantification of unlabelled and deuterium-labelled PC.

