## 7.11 Storage and analysis of clinical samples

All samples will be collected into pre-labelled containers supplied in kits for individual patients by the clinical trial team, will be double bagged and transferred in a closed container between the ICU and the processing laboratory.

- a. Baseline samples of lung TA samples will be collected up to 30 minutes before administration of the first dose of surfactant (t=0h). Samples will then be collected up to 15 minutes before the second (t=8h) and third (t=24h) doses of surfactant, at 16 hours and at 48 and 72 hours thereafter if the patient is still intubated. The TA samples will consist of blind suctioning by a cannula introduced through a port into the endotracheal tube. A volume of 20-50 ml saline will be administered, with an estimated recovery of 8-10 ml. This procedure will not interrupt the ventilator circuit and will not result in desaturation. TA samples will be taken into pre-labelled tissue culture (Falcon) tubes and stored at +4°C in the ICU sample fridge until transfer to the laboratory for processing. Transfer to the laboratory should be as rapid as possible, with a goal of under 2 hrs.
- b. Blood samples (10 ml) will be collected into EDTA vacutainers and an additional sample (9) ml will be taken and fixed in Transfix tubes. Samples will be stored at +4°C until transfer to the laboratory for processing.
- c. TA samples will be centrifuged at 400 x g x10 mins and the supernatant removed. Cell pellet differential white cell distributions will use cytopsins after fixation. Aliquots for the different assays will be prepared from the supernatant. The aliquot for lipid analysis (800 µl) will be added to ice-cold methanol in glass vials and stored at -20°C until analysis. One aliquot of supernatant (1.5 ml) will be taken for surfactant protein analysis with the remainder stored in aliquots (1 ml) in cryovials. All cryovial samples will be stored at -80±5°C until analysis.
- d. Blood samples will be centrifuged at 1200 x g x 10 mins. Two aliquots of plasma (200 µl) will be added to glass vials containing ice-cold methanol (2 ml) and stored at -20°C until lipid analysis. The remaining plasma will be stored in aliquots (500 µl) in cryovials at -80±5°C. Blood samples in Transfix tubes will be stored at +4°C.

All samples will be stored within sealed storage containers in identified secure refrigerators and freezers. Temperature of the -80°C freezers will be checked daily by a data logger.

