| Arterial Blood Gasses sampling         |                            | Samples will be taken at 0, 1, 2, 3, 6, 8, 9, 10, 11, 14, 18, 24, 25, 26, 27, 30, 36 hours |           |          |          |                |          |    |    |    |    |    |    |     |     |     |     |
| Nebuliser Administration   |                            | X                                                                                          | X         |          | X        |                |          |    |    |    |    |    |    |     |     |     |     |
| Surfactant Administration  |                            | X                                                                                          | X         |          | X        |                |          |    |    |    |    |    |    |     |     |     |     |
| Infusion of methyl-D9-choline chloride |                            | X                                                                              |           |          |          |                |          |    |    |    |    |    |    |     |     |     |     |
| Clinical Monitoring (as per SoC)       | X                          | Patients will be monitored hourly up to 32 hours post 1 st dose                 |           |          |          | X  | X        | X  | X  | X  | X  | X  | X  | X   | X   | X   | X   |
| Chest Ultrasound           | X                          | X                                                                                          | X         | X        | X        | X              | X        | X  | X  | X  | X  | X  | X  | X   | X   | X   | X   |
| Adverse event assessments              |                            | X                                                                                          | X         | X        | X        | X              | X        | X  | X  | X  | X  | X  | X  | X   | X   | X   | X   |

 Patients randomised to the treatment arm only

 Patients randomised to the treatment arm only

 Infusion of methyl-D9-choline chloride will be initiated during the stabilization period between intubation and administration of the first dose of surfactant

 4 hourly until 48 hours post first dose

 A chest ultrasound will be performed before and after each dose of surfactant. On all other occasions the chest ultrasound is performed daily.

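### Section 7.11 item 5 times the control tracer infusion at surfactant dosing, against the pre-dose window given elsewhere; followed literally, D9 labelling times would differ between arms

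*Protocol*

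**What the plan says.** The tracer is infused at 3 mg/kg over 3 hours. Its timing appears in several places in the Protocol:

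- **Section 7.11 item 5, penultimate sentence:** the infusion runs "over 3 hours after the patient is intubated and before the first surfactant administration".
- **Section 7.11 item 5, last sentence:** controls receive it "at a time equivalent to surfactant administration in the treatment group, followed by identical sample collection".
- **Section 7.7, Infusion of methyl-D9-choline chloride:** it starts in the stabilisation period before the first dose, and the reason is given: "This timing is chosen to avoid conflict with time-consuming process of surfactant nebulisation". There is no split by arm.
- **Appendix 1, footnote 5:** the infusion "will be initiated during the stabilization period between intubation and administration of the first dose of surfactant". Footnotes 3 and 4 restrict the nebuliser and surfactant rows to the treatment arm; the tracer row carries no such restriction.
- **Notes to the surfactant and D9-choline schedule:** the "infusion will commence after intubation and ventilation and typically before the first surfactant nebulization". Note 1 adds: "Surfactant will be given after a variable period of stabilization following intubation and ventilation".
- **Section 4, Control arm:** "The protocol for the control arm will be identical to the treatment arm except for surfactant nebulization".

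Tracheal aspirates are taken at 0, 8, 16, 24, 48 and 72 h (section 7.7). The table in section 3.4 gives controls the same time points. Exploratory endpoint 6 (section 3.3.3) asks whether endogenous surfactant synthesis rises sooner with treatment.

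**The concern.** Within one paragraph, the anchor for the infusion moves from before the first dose to the dose itself, and the second anchor applies to controls only. Sampling runs on the same clock in both arms. If the infusion is tied to a different point on that clock in each arm, the time available for tracer to enter phosphatidylcholine before a given sample differs by arm.

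Endpoint 6 is a question about timing, and section 7.11 item 5 uses D9-PC concentration to judge whether therapy enhances synthesis. An offset tied to arm would mix infusion timing with any drug effect. Because it is systematic, recruiting more patients would not average it out.

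The literal reading is a practical risk for two reasons. The sentence is the only visible tracer instruction addressed to controls, and staff tend to follow a specific instruction over a general one. Also, section 7.7 justifies the pre-dose slot by the need to keep clear of nebulisation. Controls have no nebulisation, so a site could take a separate control time as deliberate.

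**Working it through.** The Protocol states no figure on this point, so there is nothing to reproduce. The check is clock arithmetic under the literal reading; no kinetic model is used.

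**Inputs**
- Infusion rate: 3 mg/kg over 3 h = 1 mg/kg/h (section 7.7).
- Shared sample times T after t=0: 8, 16, 24, 48 and 72 h, plus the baseline aspirate, taken 0 to 0.5 h before the first dose (section 7.11 item a).
- Treated infusion starts at −L, where L is the lead before dosing.
- Control infusion starts at t=0 (literal reading of the last sentence of item 5).

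**The lead L is not fixed.** Item 5 puts the 3-hour infusion before dosing; if it ends exactly at dosing, L = 3 h, and longer leads are allowed. Section 7.7, Appendix 1 and the schedule notes require only that it starts before dosing, so shorter leads are possible. L = 0.5 h and L = 6 h are assumptions to show a range.

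**Time since infusion start:** treated T + L, control T. The excess relative to control is L/T.

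| Sample | Control | Treated, L = 0.5 h | Treated, L = 3 h | Treated, L = 6 h |
|---|---|---|---|---|
| 8 h | 8 h | 8.5 h (+6.3%) | 11 h (+37.5%) | 14 h (+75.0%) |
| 16 h | 16 h | 16.5 h (+3.1%) | 19 h (+18.8%) | 22 h (+37.5%) |
| 24 h | 24 h | 24.5 h (+2.1%) | 27 h (+12.5%) | 30 h (+25.0%) |
| 48 h | 48 h | 48.5 h (+1.0%) | 51 h (+6.3%) | 54 h (+12.5%) |
| 72 h | 72 h | 72.5 h (+0.7%) | 75 h (+4.2%) | 78 h (+8.3%) |

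**Time since infusion end at the 8 h sample, L = 3 h:** treated 8 + 3 − 3 = 8 h; control 8 − 3 = 5 h.

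**Tracer received by the baseline aspirate:** treated min(3, L − d) mg/kg, with d between 0 and 0.5 h; control 0.
- L = 0.5 h: 0 to 0.5 mg/kg
- L = 3 h: 2.5 to 3 mg/kg
- L = 6 h: 3 mg/kg

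**With the same window in both arms:** labelling time is T + L in each arm, so the systematic difference is 0 h at every sample, provided L is distributed alike in the two arms.

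The offset is constant in hours, so its relative weight is greatest in the early samples and small by 72 h. These are differences in timing, not estimates of a difference in D9-PC.

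**The case against.** The best defence is that the rest of the Protocol already settles the matter. Section 4 makes the arms identical apart from nebulisation, and the tracer is not nebulisation. Appendix 1 marks arm restrictions where they are meant and puts none on the tracer row. Controls have no dosing time, so the sentence in item 5 may only be setting their notional clock. The remark about nebulisation explains why the infusion precedes dosing; it does not say that controls should move. The schedule figure could not be seen and is the likeliest place for control timing to be drawn.

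Most of this stands, and it makes loose drafting the probable explanation. It does not remove the conflict: the sentence as written names surfactant administration as the anchor, and if the figure shows matched timing the sentence contradicts the figure.

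Three stronger inferences are tempting and are not supported:

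- *The offset favours surfactant, because treated patients would look labelled sooner.* The documents give no kinetics for a 3-hour infusion followed by turnover and dilution. The 0 h sample is pre-dose, so a higher treated value there is no drug effect, and in a change-from-baseline analysis it would count against treatment.
- *The baselines are not comparable in general.* Only tracer-derived D9-PC is touched. Baseline surfactant composition and concentration do not depend on the tracer, and the pool-size calculation uses the second and third surfactant doses, so it concerns treated patients only.
- *Every shared sample is certain to differ.* With a 0.5 h lead, the treated patient may have received no tracer at the baseline aspirate, and the schedule notes say only that the infusion typically precedes dosing.

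**Conclusion.** The inconsistency is real and minor. The last sentence of section 7.11 item 5 conflicts with the sentence before it, with section 7.7, with Appendix 1 footnote 5 and with the control-arm rule in section 4. A site that followed it literally would give treated patients a longer D9 labelling time than controls by the length of the pre-dose lead, and so confound the between-arm D9-PC comparison for exploratory endpoint 6.

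This rests on two assumptions: that the sentence is acted on as written, with the control infusion starting at t=0, and that treated patients have a lead above zero. The 3 h lead is illustrative. The direction and size of any effect on D9-PC cannot be derived from the Protocol. The co-primary endpoints, safety and dose decisions are unaffected.

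**What to change.** Replace the last sentence of section 7.11 item 5 with, for example: *Control patients receive methyl-D9-choline over 3 hours in the same stabilisation window after intubation, before a notional t=0 equivalent to the first surfactant dose; samples are then collected at the same times as in the treatment arm.* Check that the schedule figure agrees.

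The cost is one sentence, with no added procedure or sample. An optional, cheap addition is to record infusion start and stop times in both arms, for up to 20 patients, if the eCRF does not already hold them. Because the stabilisation period varies, this would let the comparison use actual time since infusion start.

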#### 7.12 **End of trial**

The end of study is defined as the completion of the testing of samples, to be achieved no later than 3 months after the date of the last visit of the last patient.

## 8 **TRIAL TREATMENTS**

## 8.1 Name and description of investigational medicinal product(s) and device

The AeroFact-COVID™ (AF-COVID) is an investigational drug/device combination product. The proposed indication for the AeroFact-COVID™ combination product is for the treatment of COVID-19 related Adult Respiratory Distress Syndrome (ARDS) in intubated, mechanically ventilated adults.

IMP: Bovactant (Alveofact®) is a lyophilised bovine lung surfactant presented as a lyophilized powder in 108 mg vials and reconstituted to 45 mg/mL in buffer supplied in a prefilled syringe.

Device: The nebulizer, AeroFact-COVID™ Device, is an investigational device based on the Aerogen® Solo, the market-leading vibrating mesh nebulizer for use in critical care and manufactured in Ireland by Aerogen®. It is approved in more than 75 countries and sold in excess of 2 million units in 2019.

AF-COVID combination product consists of three basic components: (i) drug, a lyophilized SFRI 1 bovine-origin surfactant and diluent for reconstitution in a vial with a reconstitution kit (marketed as Alveofact®1 by Lyomark GmbH (Germany)); (ii) reusable components: a Controller, a Synchronizer, AC/DC Adaptors and Cables; and (iii) disposable, single patient use nebulizer and respiration sensor.

Further information on Alveofact and AeroFact-COVID Device can be obtained from the Investigation Brochure and the Device Technical File.

